### Trial administration and governance

2.7

#### Sponsorship and oversight

2.7.1

The trial is sponsored by the China Medical University Hospital. The sponsors and funders have no role in the study design, data collection, management, analysis, or interpretation. A Steering Committee, composed of senior researchers in neuroscience and clinical neurology, oversees trial progress. An independent Data Management Team at China Medical University Hospital handles data auditing. A formal Data Monitoring Committee was not deemed necessary due to the non-invasive nature of the behavioral intervention in this trial. No formal interim efficacy analysis was planned, and early stopping for efficacy was not considered applicable. However, safety is monitored by the Steering Committee, whereas trial conduct is monitored quarterly by the Research Ethics Committee.

#### Participant retention and care

2.7.2

Participants may withdraw at any time upon request. The intervention may be discontinued if a participant develops a medical condition that prevents daily recitation. Participants are permitted to continue their usual medical care but are requested to avoid starting other new structured cognitive training programs during the six-month study period. To promote retention, research assistants maintain monthly contact via phone calls. This trial involves a non-invasive behavioral intervention; no specific post-trial care is required. However, any adverse events, such as MRI-related discomfort, will be assessed during follow-up visits and reported to the Research Ethics Committee, ensuring participants receive medical care at China Medical University Hospital.

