Cognitive training represents one of the most extensively studied behavioral interventions for SCD. A meta-analysis of 16 randomized controlled trials reported that cognitive training interventions were associated with improvements in individuals with SCD, with no significant statistical heterogeneity detected across studies (Bhome et al., 2018). Notably, statistically significant improvements were primarily observed when interventions were compared with non-active control groups that lacked structured cognitive stimulation (Bhome et al., 2018). This finding suggests that external cognitive engagement may be a critical factor in driving measurable benefits. Despite accumulating evidence supporting non-pharmacological approaches, research tailored to Asian populations remains limited. Among the trials included in the aforementioned meta-analysis, only one study specifically focused on individuals whose primary language was Chinese (Tsai et al., 2008). This disparity highlights a shortage of culturally and linguistically adapted cognitive intervention research for Chinese-speaking populations. In contrast to other neurological assessments, such as muscle strength evaluation, the assessment of higher cortical functions is inherently culture-dependent (Rosselli et al., 2022). For example, in the Boston Naming Test, items such as igloo and harp may be relatively unfamiliar to Chinese participants, whereas the abacus—often considered one of the more challenging items for American participants—is widely recognized among many Chinese individuals (Li et al., 2022).

More recent investigations have further demonstrated that non-pharmacological interventions, including cognitive training, transcranial direct current stimulation, balance exercises, music therapy, and mindfulness-based therapies, are associated with overall positive effects in individuals with SCD (Yu X.-H et al., 2024). However, few studies have incorporated multimodal biological assessments to elucidate the mechanistic pathways underlying observed behavioral improvements.

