The study is designed as a randomized, assessor-blinded, controlled pilot study. A stratified block randomization sequence will be generated by an independent statistician using computer-generated random numbers, with stratification by age and sex to ensure balanced group allocation. Block sizes will be randomly varied to prevent predicting upcoming assignments. Allocation concealment will be ensured using the Sequentially Numbered, Opaque, Sealed Envelopes method; envelopes will be prepared and safeguarded by personnel not involved in recruitment, eligibility assessment, or intervention delivery. After eligibility assessment and informed consent are completed, a designated research assistant — otherwise uninvolved in outcome assessment — will open the envelope to reveal group assignment. Prior to allocation disclosure, all research personnel will remain blinded to the randomization sequence. Given that the intervention is behavioral in nature, complete blinding of participants and interventionists is not feasible. However, several measures will be implemented to minimize performance bias. Participants will be instructed not to discuss their group assignment with outcome assessors. Interventionists will have no role in outcome measurement or data analysis. Outcome assessors — including neuropsychological evaluators (psychologists) and radiologic technologists — will be formally blinded to group allocation throughout the trial and will be kept separate from the intervention team. To maintain blinding integrity, assessors will be reminded of their blinded status at each assessment visit, and any unblinding events will be documented and reported. Data analysts will similarly remain blinded to group assignment until the primary analysis is complete. The inherent risk of performance bias arising from participant awareness of group assignment will be mitigated by standardizing intervention protocols, using objective outcome measures where possible, and monitoring for differential dropout between groups.

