**Figure 1 fig1:**
[figure not shown]
Workflow of the randomized controlled trial. This flowchart illustrates the recruitment, screening, and enrollment process for participants. aMIC, abbreviated Memory Inventory for the Chinese; OPD, outpatient department; SCD, subjective cognitive decline.

The intervention group will undergo structured memorization training through recitation of Chinese Classics for 6 months. The intervention will be delivered by trained research assistants in weekly 60-min sessions, supplemented by approximately 10 min of individual daily practice over the six-month period. The control group will not receive memorization training during this period. To ensure reproducibility, a detailed intervention manual has been developed specifying recitation materials, progression criteria, and instructor guidance. All instructors will complete a standardized training program prior to the commencement of the study, encompassing both the theoretical rationale for the intervention and practical delivery skills. Instructor competency will be formally assessed before authorization to deliver sessions. As this study is conducted at a single center — China Medical University Hospital — inter-center standardization is not applicable to the current protocol; however, the intervention manual will be designed to support multi-site replication in future trials.

Intervention fidelity will be monitored through the following method. Daily home practice will be tracked via automated logs within the mobile application, capturing login frequency, session duration, and task completion rates. Adherence will be operationally defined as completion of at least 80% of the designated training, including at a minimum of 80% of scheduled training sessions and the fulfillment of at least 80% of the assigned daily practice throughout the six-month duration. Participants falling below this threshold at any monthly review will be contacted by the research team to identify and address barriers to engagement.

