### Participants

2.2

Participants aged 60 years or older will be recruited, consistent with internationally recognized SCD-Initiative consensus criteria proposed by Jessen et al. (2014). Eligible individuals must report a subjective perception of cognitive decline persisting for more than 6 months and not attributable to a specific acute event, in accordance with criteria described by Molinuevo et al. (2017). SCD will be formally confirmed based on the SCD-Initiative criteria (Jessen et al., 2014), incorporating both self-report and a structured clinical interview. All participants must provide written informed consent and meet the inclusion and exclusion criteria detailed below.

Increasing evidence suggests that therapeutic interventions targeting earlier stages of neurodegenerative disease may yield greater clinical benefit compared with interventions initiated at more advanced stages. For example, disease-modifying therapies such as donanemab have been investigated primarily in individuals with early symptomatic Alzheimer’s disease (MMSE score of 20–28), reflecting the growing emphasis on early intervention (Mintun et al., 2021). Similarly, cognitive training strategies are recommended when implemented at earlier phases of cognitive decline (He et al., 2023). Based on this evidence, we selected individuals with SCD, who represent a preclinical or very early stage along the cognitive decline continuum, rather than patients with MCI. This approach allows evaluation of whether structured cognitive training may exert measurable effects prior to substantial neurodegeneration, thereby maximizing the potential sensitivity for detecting both behavioral and biological changes.

As part of the screening process, we will administer the “Abbreviated Memory Inventory for the Chinese” developed by Chinese University of Hong Kong (Lam et al., 2005). The instrument consists of five questions assessing subjective memory concerns.

Forgetting where things are placed?Unable to recall the names of good friends?Unable to follow and recall conversation?Subjective memory problems?Consider own memory to be worse than others of a similar age?

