Objective cognitive impairment defined as ≥1.5 standard deviations below standardized cognitive testing (e.g., MMSE) (Belleville et al., 2023).Diagnosis of MCI (e.g., MoCA score <26) (Sun R. et al., 2023).Clinical Dementia Rating (CDR) ≥ 0.5 (Molinuevo et al., 2017).Diagnosis of major depressive disorder (Molinuevo et al., 2017).Beck Anxiety Inventory score ≥16 (means moderate to severe anxiety).Other medical or neurological conditions that could explain cognitive decline (e.g., vascular dementia, traumatic brain injury).Claustrophobia.Contraindications of MRI (e.g., non-MRI-compatible cardiac pacemaker or devices implanted within the past 3 months).

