#### Clinical evaluations and laboratory testing

2.5.1

A structured research questionnaire will be administered to collect comprehensive baseline information, including age, biological sex, years of education, comorbidities, medication history, family history of neurodegenerative diseases, smoking and betel nut use, dietary preferences, eating habits, coffee or tea consumption (Zhang et al., 2026), bowel movement patterns, and prior experience with memorization training (e.g., structured memorization of Chinese Classics for more than 3 months). The questionnaire may be completed independently by participants or administered by trained research personnel. In addition to questionnaire-based assessments, participants will undergo basic physical examinations and detailed neurological evaluations.

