##### Statistical analysis

2.5.2.5

Statistical analyses will be conducted within the framework of the general linear model (GLM). For the primary clinical outcomes (e.g., subjective cognitive measures, neuropsychological test scores), a linear mixed-effects model will be used to handle the repeated-measures structure of the data throughout baseline, post-intervention, and follow-ups, with time, group, and group × time interaction as fixed effects, and subject as a random effect. This approach naturally accommodates missing data under the missing-at-random (MAR) assumption without requiring complete cases. The primary analysis will follow the intention-to-treat principle, including all randomized participants regardless of adherence or dropout, with missing values handled using multiple imputation based on baseline characteristics and available follow-up data. A per-protocol sensitivity analysis will also be conducted, restricted to participants who complete at least 80% of the intervention sessions. Covariates to be included in adjusted models will comprise age, sex, years of education, and baseline cognitive scores, selected *a priori* for their known associations with cognitive outcomes in SCD populations.

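### Only new outside training is discouraged and current training is no exclusion, so a control may continue a memory or recitation programme, contrary to the non-active comparator

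*Protocol article*

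**What the plan says.** The one rule on outside training is in Participant retention and care (2.7.2). Participants keep their usual medical care and are "requested to avoid starting other new structured cognitive training programs during the six-month study period". It is a request, and it covers new starts only.

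On entry, Participants (2.2) states: "All participants must provide written informed consent and meet the inclusion and exclusion criteria detailed below". The list that follows covers objective impairment, MCI, CDR, depression and anxiety, and ends with "Other medical or neurological conditions that could explain cognitive decline (e.g., vascular dementia, traumatic brain injury).Claustrophobia.Contraindications of MRI". Brain functional assessments (2.5.2) adds white matter and carotid exclusions. None of these items concerns current or past cognitive, memory or recitation training.

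On the comparator, Aims, study design, and settings (2.1) says: "The control group will not receive memorization training during this period". The Introduction reports that benefit in earlier trials was seen mainly against "non-active control groups that lacked structured cognitive stimulation". Section 2.1 adopts that type of control so that a difference is easier to detect.

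The baseline questionnaire (2.5.1) asks about "prior experience with memorization training (e.g., structured memorization of Chinese Classics for more than 3 months").

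**The concern.** The control arm was chosen for what it lacks, namely structured cognitive stimulation. The plan secures that only against programmes begun after entry. A person already enrolled in one is eligible, may be allocated to control, and breaks no stated rule by carrying on.

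A stated aim in section 2.1 is to estimate effect sizes for sizing a definitive trial. If some controls are being trained elsewhere, the between-arm difference could be attenuated and a later trial planned on too small an effect. The anticipated secondary outcome (3.3) could be touched as well. It reads lower fronto-striatal activation during recitation as the result of practice, and outside recitation could produce the same in a control.

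The questionnaire item shows that the exposure was foreseen. However, it asks about prior experience, not ongoing participation. Nor is it among the stratification factors ("with stratification by age and sex to ensure balanced group allocation") or the named covariates ("age, sex, years of education, and baseline cognitive scores").

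**Working it through.** **Passages side by side.**
- Entry criteria (2.2, 2.5.2): silent on current training.
- Conduct rule (2.7.2): limits new starts only.
- Control condition (2.1): no memorization training. Read as a condition on controls, neither the entry criteria nor the conduct rule enforces it. Read as a description of what the trial provides, it does not make the arm non-active.
- Contamination (3.2): acknowledged only through social contact with intervention participants.

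**Reproducing the plan's figure.** Sample size (2.3) gives 383 per group for d = 0.18, one-sided α = 0.05 and power 0.80. The normal approximation is n = 2(z₀.₉₅ + z₀.₈₀)²/d² = 2(1.645 + 0.842)²/0.18² ≈ 382. The exact noncentral-t calculation gives 383 with power 0.8006. The figure is right and serves below only as a base for illustration.

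**Dilution.** Let p be the share of controls already in outside training (an assumption; no document gives it). If that training is fully equivalent, the observed effect is d(1 − p) and the derived sample size is multiplied by 1/(1 − p)².

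| p (assumed) | d(1 − p) | 1/(1 − p)² | n per group (exact t) |
|---|---|---|---|
| 0 | 0.180 | 1.00 | 383 |
| 5% | 0.171 | 1.11 | 424 |
| 10% | 0.162 | 1.23 | 472 |
| 20% | 0.144 | 1.56 | 597 |

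Full equivalence makes these the largest values for each p. If outside training yields only a fraction e of the effect, the factor is 1 − pe. With p = 10% and e = 0.5 it is 1 − 0.05 = 0.95, and the inflation is 1/0.95² = 1.11 instead of 1.23.

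**Chance that it occurs at all.** With 30 controls, the probability of at least one such person is 1 − 0.95³⁰ = 79% if 5% of eligible people are in such training, and 1 − 0.90³⁰ = 96% if 10% are.

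**Against the pilot's precision.** With 30 per arm, the 95% confidence interval for d has a half-width of about 1.96 × √(2/30) = 0.51. At d = 0.18 the shift is 0.18 × 0.10 = 0.018 for p = 10% and 0.18 × 0.20 = 0.036 for p = 20%. Both are small next to 0.51.

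**The case against.** The strongest reply is that this is a usual-activity comparator: existing habits are left alone, randomisation spreads them over both arms, and the trial estimates the effect of adding recitation to ordinary life. That is a coherent estimand, but not the one section 2.1 chose. Its argument rests on controls without structured stimulation.

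A second reply is that the sentence on controls in section 2.1 already bars memorization from any source. It can be read so, and the recitation case is then covered in principle. No entry criterion or conduct rule carries it out, and other cognitive training stays uncovered.

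Third, the list in 2.2 is not complete, since 2.5.2 adds exclusions, and the full protocol may hold one on current training. If it does, a rule on new starts would be sufficient. The article, however, presents its criteria as those that participants must meet, and nothing in it points to such a rule. How the questionnaire item enters the analysis may fairly be left to an analysis plan, but the item would still miss ongoing participation.

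Fourth, dilution may be slight. The anticipated primary outcome is change from baseline to six months. Someone long settled in another activity may gain little more as a control, yet still respond to a new programme. This stands, and it is why the table shows maxima.

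A reader might go further and infer that controls are likely to be in recitation classes because recruitment also uses community activity centers (3.2). The documents do not support that. They do not say that these centers run such classes, and the Introduction calls culturally matched programmes scarce.

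**Conclusion.** The inconsistency stands. As written, a person already in structured cognitive, memory or recitation training can enter, be allocated to control and continue, which does not fit the described control condition or the reason for choosing it. The result could be an attenuated effect estimate.

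The size cannot be derived from the documents. The range of 1.11 to 1.56 rests on an assumed 5% to 20% of controls and on full equivalence of outside training, so it is a ceiling for those shares and not an estimate. A reader might infer an established bias toward zero of known size; the documents support only a possible attenuation of unknown size. It is also small beside the imprecision of 30 per arm, in a pilot that calls its estimates preliminary and, in the Introduction, puts feasibility and acceptability first. The sample-size arithmetic is unaffected. Severity is minor to moderate, and the case for acting rests largely on how cheap the remedy is.

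**What to change.** 1. Add to the exclusion criteria in Participants (2.2): current participation in a structured cognitive, memory or recitation programme. No fixed look-back period is needed. The three months in the questionnaire item describe how long past training lasted, not how recent it was, and give no basis for a washout.
2. Reword the rule in Participant retention and care (2.7.2) so that participants are asked not to take part in any other structured cognitive training, memory and recitation classes included, up to the six-month assessment. It then agrees with the control condition in section 2.1.
3. Record any outside training in both arms at the monthly calls already planned, so that remaining exposure can be described.

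The cost is a protocol amendment, one screening question next to an existing questionnaire item, and one question per call. The downside is a few recruits lost and slightly slower accrual, in a trial that already expects recruitment to be difficult (3.2).

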**Methods:**

A total of 60 individuals with subjective cognitive decline will be enrolled in a randomized, assessor-blinded, controlled pilot study. Participants will be randomly assigned to either an intervention group or a non-active control group prior to baseline assessment. The intervention group will undergo a six-month structured recitation training program. Both groups will undergo short-term follow-up after the intervention, and long-term follow-up annually post-intervention. Multimodal assessments will include neuropsychological testing, functional magnetic resonance imaging (fMRI), electroencephalography (EEG), blood biomarker profiling, gut microbiota analysis, and fecal metabolomics.

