Following completion of the initial six-month intervention phase, participants will be given the option to voluntarily continue recitation practice. The selection of a six-month intervention period is informed by the MEMO+ (Méthode d’Entrainement pour Mémoire Optimale) protocol developed by Sylvie Belleville and colleagues (Bier et al., 2015). Later studies from the same research team have demonstrated that participants receiving structured cognitive training exhibited significant improvements in memory recall performance, with effects persisting for at least 6 months post-intervention (Belleville et al., 2018). Furthermore, long-term follow-up over 5 years revealed that individuals who had undergone cognitive training experienced a slower decline in delayed memory performance and Montreal Cognitive Assessment (MoCA) scores compared with control groups (Belleville et al., 2024). These findings underscore the sustained benefits and potential long-term impact of continuous cognitive training.

Additional support for the selected intervention duration is derived from studies examining other forms of cognitively engaging activities. For example, interventions involving structured calligraphy practice have demonstrated that extending training duration over a six-month period leads to significant alterations in functional brain connectivity (Lee et al., 2024). Specifically, increased connectivity has been observed between the medial prefrontal cortex (mPFC) and right lateral temporal cortex (LTC), mPFC and right inferior parietal lobe (IPL), left hippocampal formation (HF) and right LTC, as well as between the left HF and right IPL (Lee et al., 2024). These findings suggest that prolonged engagement (6 months) in cognitively demanding tasks may induce measurable neuro-modulatory effects at the network level.

Taken together, a 6-month intervention period represents a balanced design choice: it is sufficiently long to allow for detectable behavioral and neurobiological changes, yet not so prolonged as to compromise participant adherence. Accordingly, outcome assessments will be conducted at baseline (time of recruitment), immediately after the six-month intervention, and at one-year and two-year follow-ups, with annual assessments thereafter until participants are no longer able to complete evaluations. The study will be conducted at China Medical University Hospital, primarily within the outpatient clinics of the Departments of Neurology or Psychiatry.

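### No adverse-event assessment is stated during the six-month intervention, and no route takes adverse-event reports to the committee named as safety monitor

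*Protocol article*

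**What the plan says.** Four parts of the protocol article bear on this.

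- **Occasion and recipient (2.7.2, Participant retention and care).** "any adverse events, such as MRI-related discomfort, will be assessed during follow-up visits and reported to the Research Ethics Committee".
- **Visit schedule (2.1, Aims, study design, and settings).** "outcome assessments will be conducted at baseline (time of recruitment), immediately after the six-month intervention, and at one-year and two-year follow-ups", then yearly. The abstract describes the later visits as "long-term follow-up annually post-intervention".
- **Oversight (2.7.1, Sponsorship and oversight).** "A formal Data Monitoring Committee was not deemed necessary due to the non-invasive nature of the behavioral intervention in this trial". The same section adds that "safety is monitored by the Steering Committee, whereas trial conduct is monitored quarterly by the Research Ethics Committee".
- **Contacts between visits.** Section 2.7.2 states: "To promote retention, research assistants maintain monthly contact via phone calls". Section 2.1 adds, for the intervention arm, "The intervention will be delivered by trained research assistants in weekly 60-min sessions". Of the other arm it says "The control group will not receive memorization training during this period". Section 2.1 also has home practice logged by the mobile application, and participants contacted when a monthly review finds them below the 80% adherence threshold. None of these contacts is said to collect adverse events.

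**The concern.** Exposure to the intervention lasts six months, and the one stated occasion for assessing adverse events after baseline falls at its end. An event early in training would be reported from memory months later. Feasibility and acceptability are the primary aim, and how well people aged 60 or older tolerate daily practice bears on acceptability. Six-month recall is weak evidence for that.

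The second part is governance. The Steering Committee monitors safety and there is no Data Monitoring Committee, yet the only stated recipient of adverse-event reports is the Research Ethics Committee, to which section 2.7.1 assigns trial conduct. A reader cannot tell from the article how the safety monitor obtains its data.

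**Working it through.** The protocol gives no figure on this point to reproduce, and no adverse-event rate. The check is therefore of timing and of how the sections fit together.

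**1. Visit gaps.** The schedule in section 2.1 can be read in two ways.
- One-year visit counted from baseline: months 0, 6, 12, 24, 36. The gaps are 6, 6, 12 and 12 months.
- Yearly visits counted from the end of the intervention, as in the abstract: months 0, 6, 18, 30. The gaps are 6, 12 and 12 months.

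On either reading visits are 6 to 12 months apart, and no visit falls between baseline and month 6.

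**2. Delay from onset to stated assessment during exposure.** Assume onset is evenly spread over the gap between assessments. Then mean delay = gap / 2 and maximum delay = gap.
- Visits as stated: mean 6 / 2 = 3 months, maximum 6 months.
- Monthly calls used for this purpose: mean 1 / 2 = 0.5 month, maximum about 1 month.

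The maximum does not depend on the even-onset assumption; the mean does. The monthly figures assume that the calls reach both arms. Section 2.7.2 states no restriction by arm.

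**3. Opportunities to volunteer an event in months 0 to 6.** Take 26 weeks and 6 monthly calls.
- Intervention arm: 26 sessions + 6 calls = 32 contacts.
- Control arm: 6 calls.
- Ratio: 32 / 6 = 5.3.

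This counts contacts. It does not measure bias, and it matters only if volunteered events are recorded alongside those found at visits.

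**4. Sections 2.7.1 and 2.7.2 side by side.**

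| | Steering Committee | Research Ethics Committee |
|---|---|---|
| Role in 2.7.1 | Monitors safety | Monitors trial conduct, quarterly |
| Stated recipient of adverse-event reports in 2.7.2 | Not mentioned | Yes |

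Both statements can be true together. What is missing is the sentence that joins them.

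**The case against.** The strongest reply is that the text never says that adverse events are assessed only at visits, that the calls serve only retention, or that reports go only to the ethics committee. A condensed article may leave forms, timing and routing to the full protocol. This stands in part: definitions, grading and forms are rightly not raised here. But the article does choose an occasion and a recipient, and it gives the calls a different purpose. The point concerns what it states.

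A reader might infer that the arms cannot be compared fairly. The documents do not support that. Visits follow one schedule in both arms, so late recording and poor recall affect both alike. The contact ratio becomes relevant only if events volunteered at weekly sessions are counted, and no section says that they are. Nor is a between-arm analysis of harms planned: none appears among the aims, the outcomes in 2.5 or the analyses in 2.5.2.5 and 2.6.

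A reader might also infer that the two governance sections contradict each other, or that the Steering Committee will have no safety data. Reporting to one body does not exclude reporting to another, so neither inference holds.

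Finally, it might seem that a condition preventing recitation, which section 2.7.2 gives as a ground for discontinuation, would go unseen between visits. Sections 2.1 and 3.2 make this unlikely. Practice is logged automatically, shortfalls lead to contact, and reasons for non-adherence and dropout are documented. Such a condition would probably surface within about a month. That route is tied to training adherence, so it does not cover the control arm or events that leave practice unaffected.

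**Conclusion.** The point holds in limited form. As written, no adverse-event assessment is stated during exposure, and events in that period may be recorded up to 6 months after onset, or 3 months on average with even onset. No route is stated from adverse-event reports to the committee named as safety monitor, and the two sections should be reconciled.

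The stated method is symmetric between arms. Unequal ascertainment is conditional on counting events volunteered at the weekly sessions. Severity is minor: the intervention is a low-risk behavioral one and no harms comparison is planned. It is still worth changing, because a better method is available through contacts that already exist.

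**What to change.** - **Section 2.7.2, collection.** State that during months 0 to 6 the existing monthly calls put the same short adverse-event questions to both arms, and that the same questions continue at the follow-up visits.
- **Section 2.7.2, summary.** State that any between-arm summary of harms uses these solicited reports, and that events volunteered at the weekly sessions are listed separately.
- **Sections 2.7.1 and 2.7.2, routing.** Reconcile the two so that the body named as safety monitor also receives the adverse-event reports.

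The cost is a few minutes per call, one short form and a wording amendment. No visits or staff are added, since research assistants already make the calls. The downside is that slightly more minor events will be recorded.
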